### Data analysis

2.7

Preliminary data analysis is scheduled for early November 2025, while the final results will be available at the end of the study. The results will be published within one year after the conclusion of the study.

#### Quantitative analysis

2.7.1

Statistical data processing will be conducted via R software, version 4.0.0 (RStudio Team, 2020), IBM SPSS Statistics (IBM Corp, 2020), Stata17 (StataCorp, 2021), and JASP (Jasp Team, 2024).

Categorical variables will be summarized through absolute and percentage frequency distributions, and quantitative variables through appropriate centrality and variability indices.

Descriptive analyses will be calculated for both the psychological variables (depressive symptoms, psychological flexibility and quality of life) and the usability (UX) and user involvement (UE) variables. These analyses will be performed on the variables analyzed at the beginning, during and at the end of the interaction with REA.

The relationships between variables will be analyzed mainly through *ad-hoc* statistical tests, such as the chi-square test, Fisher’s exact test, t-test for paired data or Wilcoxon’s nonparametric tests and the sign test (based on an assessment of compliance with assumptions) to understand the differences between the beginning and the end of the path in the same study sample to the variables under investigation.

In addition, univariate logistic or multinomial regression models will be presented. Finally, to eliminate possible confounding factors, multiple regression models will be proposed in which the effects of the explanatory variables on the outcome variables will be adjusted for possible confounders. For each analysis, statistical significance will be found with a p-value ≤.05.

Multivariate models will include adjustment for potential confounders collected in the protocol, including maternal age, educational attainment, employment status, marital status, previous pregnancies/births (parity), gestational age at enrolment, baseline CES-D, MPFI and SF-12 scores. The extant literature identifies these variables as being associated with perinatal mental well-being and adherence to digital solutions. Sensitivity analyses will explore the robustness of the results with respect to different model specifications and the availability of wearable data (steps, sleep, HR) as exploratory covariates.

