#### Secondary outcomes and follow-up

2.4.2

The variable expressing the outcome ‘psychological well-being’ will be assessed by administering the 4 self-report questionnaires, namely the two Whooley’s Questions (24), the Centre for Epidemiological Studies-Depression Scale (25), the Multidimensional Psychological Flexibility Inventory (26) and the 12-Item Short Form Survey (27) at the beginning and end of the psychoeducational intervention (refer to **Table 1** for a detailed overview of the questionnaire adopted). The endpoints to be measured are as follows: a score of the individual items of the questionnaires, the average score of the questionnaires, and the difference between the average score values of the individual questionnaires at the different survey times. At the follow-up appointment, which takes place two months after childbirth, Whooley’s Questions will be administered. If the participant confirms her willingness, the CES-D will also be administered to assess the risk of PPD.

**Table 1 T1:** Summary of the questionnaires administered and their timing.

Screening	At the beginning of the study (week 0)	At the end of week 3	At the end of the study (week 6)	Follow-up (2 months after birth)
Whooley’s Questions	–	–	–	Whooley’s Questions
–	CES-D^a^	–	CES-D	CES-D
–	MPFI^b^	–	MPFI	–
–	SF-12^c^	–	SF-12	–
–	–	SUS^d^	SUS*	–
–	–	ITA BUS B^e^	ITA BUS B*	–
–	–	–	UES-SF^f^*	–
–	–	–	uMARS^g^*	–
–	–	–	–	Qualitative interview
				

a CES-D, Center of Epidemiological Studies-Depression Scale.

b MPFI, Multidimensional Psychological Flexibility Inventory.

c SF-12, Short Form Health Survey 12.

d SUS, System Usability Scale.

e ITA BUS B, Chatbot Usability Scale, version B.

f UES-SF, User Engagement Scale-Short Form.

g uMARS, User Mobile Application Rating Scale.

*These usability questionnaires will be administered the following day, so as not to burden the participant during completion.

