### Sample size

2.6

The present research project is a proof-of-concept study, in which a limited sample is sufficient to achieve the intended aims.

If non-parametric statistics are conducted (assuming that the distribution is not normal), the sample should consist of N = 24 pregnant women with Bonferroni correction (α = .025).

The sample size and power for nonparametric tests (Kruskal-Wallis Test, Wilcoxon *post-hoc* test) were calculated according to Noether (40).

If parametric statistics are conducted (assuming that the distribution is normal), the sample must instead consist of 41 pregnant women with Bonferroni correction (α = .025).

Therefore, setting the power level at.80 and the significance level at.025 and taking into account a 20% possible drop-out, a total of 50 pregnant women were estimated to need to be recruited in order to carry out the study.

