## Expected results

3

The psychoeducational pathway is expected to yield significant results, primarily in terms of women’s satisfaction and engagement with the use of the innovative digital solutions (SUS ≥ 68; average UES-SF ≥ 3.5/5; ITA BUS B ≥ 44/55; uMARS ≥ 4/5). Thresholds for usability and engagement were pre−specified based on established interpretive benchmarks and validated scale ranges: SUS ≥68 reflects above−average usability; UES−SF ≥3.5/5 indicates engagement above the neutral midpoint; ITA BUS B ≥44/55 corresponds to an average item agreement of ≥4/5; and uMARS ≥4/5 denotes high app quality. These targets are consistent with guidance and validation for the respective instruments (28–31).

We anticipate an increase between pre- and post-intervention in the levels of psychological well-being, quality of life of the woman and psychological flexibility. Specifically, we hypothesize: (i) an increase in MPFI psychological flexibility, (ii) an improvement in the mental component of the SF-12, (iii) a reduction in CES-D. These outcomes are exploratory and consistent with the main objective of assessing the acceptability, feasibility, and UX/UE of the intervention. It is important to highlight that, on the one hand, REA can be a valuable resource in ensuring regular psychoeducational support for women during the perinatal period. On the other hand, the literature has shown that women during the perinatal period indicated a preference for support provided online, suggesting that the implementation of digital interventions can overcome barriers around social stigma and reluctance to seek help.

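### The sample size assumes a Bonferroni-corrected level of .025, but the analysis section declares significance at .05 throughout, so the correction is never applied

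*Protocol article*

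**What the plan says.** Section 2.6 (Sample size) gives two sample sizes, 24 women for non-parametric tests and 41 for parametric tests. Each is tied to a Bonferroni correction with α = .025. The level appears a third time where the total is derived: "setting the power level at.80 and the significance level at.025 and taking into account a 20% possible drop-out", leading to "a total of 50 pregnant women were estimated to need to be recruited in order to carry out the study".

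Section 2.7.1 (Quantitative analysis) lists chi-square, Fisher, paired t, Wilcoxon and sign tests and several regression models. It closes the description of these with one rule: "For each analysis, statistical significance will be found with a p-value ≤.05". It mentions no Bonferroni correction, no adjusted p-values and no subset of tests held to a stricter level.

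The article does not say which two comparisons the .025 level is meant to cover.

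**The concern.** A Bonferroni correction only works if the corrected level is used when the tests are judged. Here it is used to justify the number of women recruited and then disappears from the rule for declaring significance. An analyst cannot follow both sections. For any comparison inside the corrected family, a p-value in the band from .025 to .05 gets opposite labels depending on which section is read, and the choice could be made after the data are seen.

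What is at stake is the labelling of pre-post changes in an uncontrolled study that already anticipates improvement. This cannot be left to a later analysis plan as a detail, because no such plan could comply with both sentences as they stand.

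**Working it through.** **Inputs from the documents.** Section 2.6: α = .025 with Bonferroni correction, power .80, drop-out 20%, N = 24 (non-parametric) or 41 (parametric), total 50. Section 2.7.1: p ≤ .05 for every analysis.

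**Inputs not in the documents.** Effect size and sidedness are not given. Where needed, I assume two-sided tests and show a range for the standardised paired difference d.

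**1. The corrected level.** .05 / 2 = .025. The stated level is that of a Bonferroni correction for two tests at an overall .05.

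**2. The plan's own sample size.**
- Total: 41 × 1.2 = 49.2, rounded up to 50, as stated. (Dividing by the retention rate gives 41 / 0.8 = 51.25, or 52. That difference does not bear on this point.)
- N = 41: a two-sided paired t-test (exact noncentral t) at α = .025 and power .80 gives the following.

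| Assumed d | N at α = .025 | N at α = .05 |
|---|---|---|
| 0.40 | 62 | 52 |
| 0.45 | 50 | 41 |
| 0.50 | 41 | 34 |
| 0.60 | 29 | 24 |

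The stated 41 is reproduced at .025 with d = 0.50. It would also arise at .05 with d = 0.45, so the number alone does not show which level was used; the text of section 2.6 does.
- N = 24: Noether's formula at two-sided .025 would need a probability of about 0.863 (signed-rank) or 0.815 (sign test). Neither is stated, so 24 cannot be checked.

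**3. Family-wise error for two tests, all nulls true.** Under independence the error is 1 − (1 − α)²; the Bonferroni bound is 2α.
- At .05 (section 2.7.1): 1 − 0.95² = 0.0975; bound 2 × .05 = .10.
- At .025 (section 2.6): 1 − 0.975² = 0.0494; bound 2 × .025 = .05.

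If the two tests were completely dependent, the error would fall to that of a single test, .05 and .025 respectively. Under positive dependence the figure at .05 therefore lies between 5% and 9.75%; under any dependence it cannot exceed 10%.

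**4. The disputed band.** For one test with a true null, the chance of a p-value between .025 and .05 is .05 − .025 = .025, or 1 in 40.

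**5. Effect on power.** With 41 women and the assumed d = 0.50, power is 0.805 at .025 and 0.878 at .05. Testing at the looser level raises power.

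**The case against.** The strongest case on the other side is that little depends on the choice. The primary outcomes are user experience and engagement, and their targets in section 3 are score thresholds (SUS ≥ 68, UES-SF ≥ 3.5, ITA BUS B ≥ 44, uMARS ≥ 4), not p-values. The psychological outcomes are secondary, and section 3 calls them exploratory. The Discussion concedes that a pre-post change might not be due to the intervention, and the Limitations section disclaims any test of effectiveness. All of this stands and lowers the severity. It does not remove the conflict: if the tests are exploratory, a blanket significance rule does not fit them either.

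One could also read p ≤ .05 as applying to Bonferroni-adjusted p-values, which would remove the conflict. Nothing in section 2.7.1 supports that reading.

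Three stronger readings are tempting, and the documents do not support them:

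- **A factor of two is wrong because there are three hypotheses.** Section 3 says "we hypothesize: (i) an increase in MPFI psychological flexibility, (ii) an improvement in the mental component of the SF-12, (iii) a reduction in CES-D". But these are exploratory secondary hypotheses, and nothing identifies them as the corrected family. The two primary constructs, or time-point comparisons, could equally give a factor of two. Neither is confirmed, and so the family has to be named.
- **Item-level testing would produce many false positives.** Section 2.4.2 lists "a score of the individual items of the questionnaires, the average score of the questionnaires" as endpoints, but the difference endpoints in sections 2.4.1 and 2.4.2 are defined on average questionnaire scores. No item-by-item significance tests are planned.
- **False signals would drive the later randomised trial.** The article calls for that trial whatever the results, and states no progression rule based on p-values.

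**Conclusion.** The contradiction is real: the article states a corrected level of .025 for sizing and an uncorrected level of .05 for deciding. For the two tests that the correction implies, the family-wise error is 9.75% instead of 4.94% under independence with all nulls true. The bounds, which need no independence, are 10% and 5%.

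The consequence is confined to which pre-post results may be called significant. Power is not reduced and no confirmatory conclusion depends on it. Severity is moderate. A reader might infer that the sample size is also invalid, but this conflict does not show that, because 41 and 50 are stated for the stricter level.

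**What to change.** In section 2.7.1, replace the single blanket rule. Name the two comparisons that the .025 level covers, and state that they are judged at p ≤ .025 or, equivalently, at a Bonferroni-adjusted p ≤ .05 (twice the raw p-value). State that p-values from all other analyses are exploratory or descriptive.

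This is a wording change, best made before the data are analysed. It leaves the planned 50 women unchanged, because that number already assumes .025. For two tests, it brings the family-wise error back to 4.94% under independence, and to at most 5% in any case. The downside is that fewer results can be labelled significant: for the two named comparisons, power at 41 women would be about 0.805 instead of 0.878 under the assumed d = 0.50, which is still the power the plan set out to have.

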### Risks and mitigations

3.1

Possible critical issues that may arise during the study include: (i) low adherence to the program (mitigation: in-app reminders and flexibility of use); (ii) digital overload (mitigation: short sessions ≈20 minutes, alternating formats, burden monitoring); (iii) emergence or worsening of symptoms during the intervention (mitigation: upstream exclusion via Whooley, clear messages on help channels, clinical escalation where necessary); (iv) selection/adherence bias (mitigation: detailed description of the sample and sensitivity analysis); (v) limitations of wearable data (mitigation: use for exploratory triangulation, not causal inferences).

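### The sensitivity analysis promised against selection and adherence bias is not among those described, so the pre-post changes in CES-D, MPFI and SF-12 describe completers with no check on drop-out

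*Protocol article*

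**What the plan says.** Section 2.7.1 (Quantitative analysis) compares start and end scores by a paired t-test, Wilcoxon tests or the sign test, with the aim "to understand the differences between the beginning and the end of the path in the same study sample". It then describes the sensitivity analyses: "Sensitivity analyses will explore the robustness of the results with respect to different model specifications and the availability of wearable data", with steps, sleep and heart rate as exploratory covariates.

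Section 3.1 (Risks and mitigations) lists "selection/adherence bias (mitigation: detailed description of the sample and sensitivity analysis". It gives no method for that sensitivity analysis. It lists low adherence and the emergence or worsening of symptoms as separate risks.

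Section 2.6 (Sample size) allows for loss: "taking into account a 20% possible drop-out, a total of 50 pregnant women were estimated to need to be recruited".

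Section 3 (Expected results) states directional hypotheses (MPFI flexibility and the SF-12 mental component up, CES-D down) and calls these outcomes exploratory.

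**The concern.** The secondary objective concerns well-being before and after the programme in the women who take part. A paired test leaves out every woman without an end score, so it estimates the change among those who finished. The two groups give the same answer only if women who leave change, on average, as those who stay.

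The plan recognises this kind of risk in section 3.1 and relies on a sensitivity analysis to meet it. The checks described in section 2.7.1 cannot do that job. A different model specification fitted to women with both scores is still fitted to completers. A model with wearable covariates may use fewer women still, because section 2.5 makes the smartwatch optional. Both checks could agree closely with the main result whatever happened to the women who left.

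At stake is the size of the preliminary pre-post signal that section 4 describes ahead of a later randomised trial.

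**Working it through.** **Inputs from the documents.** Recruited N = 50, drop-out 20%, 41 evaluable women in the parametric case, 24 in the non-parametric case, power 0.80, α = 0.025 (all section 2.6).

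**Inputs not in the documents.** The effect size, the sidedness of the test, and how drop-outs change. These are assumptions below.

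**1. The plan's own figures.** For a paired t-test with two-sided α = 0.025 and an assumed standardised change of 0.5, the exact noncentral-t calculation gives n = 41 (power 0.805), which matches "the sample must instead consist of 41 pregnant women with Bonferroni correction (α = .025". Inflating by 20%: 41 × 1.2 = 49.2, rounded up to 50, which matches the plan. Division by the retained share would give 41 / 0.8 = 51.25, or 52; the difference is small. The non-parametric 24 cannot be checked, because the effect needed for Noether's formula is not given.

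**2. Women lost.** 50 × 0.8 = 40 completers and 10 women without an end score.

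**3. Completer change against all-enrolled change.** Let d be the drop-out proportion and r the mean change in drop-outs divided by the mean change in completers, with improvement counted as positive.

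- All-enrolled change / completer change = (1 − d) + d·r
- Overstatement by the completer mean = 1 / [(1 − d) + d·r] − 1

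With d = 0.20:

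| Drop-outs (assumed) | r | All-enrolled / completer | Overstatement |
|---|---|---|---|
| change as completers do | 1 | 1.00 | 0% |
| change half as much | 0.5 | 0.90 | 11% |
| do not change | 0 | 0.80 | 25% |
| worsen by half the completer change | −0.5 | 0.70 | 43% |
| worsen by all of the completer change | −1 | 0.60 | 67% |

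If r exceeds 1, the completer mean understates the all-enrolled change.

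**4. Other drop-out rates, r = 0.** At 10%: 1 / 0.9 − 1 = 11%. At 30%: 1 / 0.7 − 1 = 43%.

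**5. On an SD scale.** If completers improve by the assumed 0.5 SD, the last three rows correspond to drop-outs changing by 0, −0.25 and −0.5 SD, and to all-enrolled changes of 0.40, 0.35 and 0.30 SD. The percentages themselves do not depend on the 0.5.

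**The case against.** The strongest objection is that this is an omission from a condensed article. No complete-case rule is written, the list of tests is introduced as examples, and missing-data handling usually belongs in the full protocol or analysis plan, which are not shown. Section 2.7.1 does not say its sensitivity analyses are the only ones. This has weight, and the absence of a missing-data policy alone would not be a finding. What stands is narrower: the article names a specific risk, names a sensitivity analysis as the protection, and then describes sensitivity analyses that cannot provide it. Every test it names for the start-to-end comparison needs both scores.

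A second objection concerns direction. A reader might infer that women who feel worse are the ones who leave, so that the changes are overstated by at least a quarter. The documents do not support that. Section 3.1 does not link worsening to drop-out, women enter with negative Whooley questions, and the programme runs through late pregnancy and past delivery, so loss unrelated to mood is plausible. Nor does the article say that a woman who stops sessions is not sent the end questionnaires. Section 2.7.1 does say that its adjustment variables, including the baseline scores, are associated with both well-being and adherence. That makes informative loss possible but does not fix its sign.

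Third, the outcomes are secondary and exploratory, there is no control group, and sections 4 and 4.1 disclaim effectiveness. This limits the harm. It does not answer the point, because lack of a control group and loss of participants are separate sources of bias, and the limitations section discusses only the first.

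**Conclusion.** The mismatch holds. The mitigation promised in section 3.1 is not delivered by the sensitivity analyses in section 2.7.1, and the paired results would describe only women with both scores. At the planned 20% drop-out the completer mean change exceeds the all-enrolled change by 0%, 11% or 25% as drop-outs change equally, half as much or not at all, and by 43% to 67% if they worsen by half to all of the completer change. The 25% figure is one scenario in a range that starts at zero; it is not a floor. The result rests on the planning allowance for drop-out and on assumed behaviour of drop-outs, and the direction of bias is itself an assumption. The consequence is confined to an exploratory, uncontrolled pre-post estimate. The primary user-experience and engagement outcomes are outside this point.

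**What to change.** In section 2.7.1, specify the sensitivity analysis that section 3.1 promises:

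- State that the paired tests describe women with both a start and an end score, and report how many that is out of all enrolled.
- Compare baseline CES-D, MPFI and SF-12 between women with and without an end score.
- Beside each paired result, report the mean change for all women with a baseline score, first assuming no change in women without an end score, then under one or more worsening values stated in advance (for example half and all of the completer change).

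Multiple imputation can be optional. With about 10 women to impute and many covariates it may be unstable.

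The extra estimates should be reported as descriptions, not used as a significance test. With 40 completers, mean 0.5 and SD 1, t = 0.5 / (1/√40) ≈ 3.16. Adding 10 zeros gives mean 0.40, SD √[(39 + 40 × 0.25 − 50 × 0.16) / 49] ≈ 0.915, and t ≈ 3.09. Filling in zeros shrinks the SD and raises n, so significance hardly moves while the mean falls by a fifth.

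The cost is a few sentences, a few hours of analysis on data already collected, and possibly a less favourable exploratory estimate.

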#### Qualitative analysis

2.7.2

About the analysis of the semi-structured interviews, a text mining approach (35) will be used to extract the answers that appear repeatedly from the interviews that will be conducted concerning the women’s experience of interacting with REA and with respect to how they felt throughout the process.

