### Goal of the study and research questions

1.3

The intervention is designed to enhance the improvement of women’s psychological well-being by helping them manage stressful situations more effectively through modules based on ACT principles and to prevent postpartum distress. The study also envisages collecting and using data from wearable devices (smartwatches, CE-marked and GDPR compliant) for triangulation with objective parameters (such as sleep quality or physical activity level) to support the women’s self-reported data.

The primary objectives of this proof-of-concept study are (1) to explore the User Experience (UX) and User Engagement (UE) of women interacting with the TreC Mamma application and the virtual coach, REA and (2) to assess, through semi structured interviews, participants’ experience with both REA and the application, as well as their emotional responses throughout the intervention.

The secondary objectives are to assess psychological well-being before and after the intervention, to administer self-assessment questionnaires at the beginning and end of the psychoeducational program, and to analyze the data collected via wearable devices. It is important to emphasize that the data collected from smartwatches on steps, sleep and heart rate are objective indicators of behavior and physiological status, and are used to triangulate self-reports. This data has exploratory and non-causal value.

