### Design and setting

2.1

REA, the virtual coach developed within the TreC Mamma application, will interact with women for 8 weeks starting from week 25/30 of pregnancy, with one month between the end of session 6 and the beginning of session 7.

Specifically, there will be one psychoeducational session per week with integrated exercises. The woman can choose the day and time that best suits her needs to interact with REA.

At the beginning of the course, REA will administer the 4 self-report questionnaires, namely the two Whooley’s Questions (24), the Centre for Epidemiological Studies-Depression Scale (CES-D) (25), the Multidimensional Psychological Flexibility Inventory (MPFI) (26) and the 12-Item Short Form Survey (SF-12) (27) to establish the baseline level.

After the data collection phase, the intervention will be administered, and its contents will be presented in different formats (text, images, audio, and video tracks).

The questionnaires will be further administered at the end of the intervention to assess whether the women perceived a change in psychological well-being and quality of life. These data will then be triangulated with the parameters collected by the smartwatch.

Four questionnaires will be administered in order to assess usability: User Experience (UX) and User Engagement (UE). Usability and engagement measures include the User Engagement Scale Short-form (UES-SF) (28), the System Usability Scale (SUS) (29), the Italian version of the Chatbot Usability Scale (ITA BUS B) (30), and the User Mobile Application Rating Scale (uMARS) (31). The questionnaires are managed by a microservice within the TreC platform that complies with the requirements and regulations in terms of personal data protection.

After two months, women who have given consent will be undergoing a semistructured interview in order to investigate their experience in using REA and the TreC Mamma application, and to understand how the women felt during the process.

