#### Primary outcomes

2.4.1

The primary outcomes are UX and UE. They will be assessed via questionnaires, namely the User Engagement Scale Short-form (UES-SF) (28), the System Usability Scale (SUS) (29), the Italian version of the Chatbot Usability Scale (ITA BUS B) (30), and the User Mobile Application Rating Scale (uMARS) (31), which will be administered at different time slots through the study, in particular the usability questionnaires will be administered at the end of the third (3 questionnaires) and sixth (end of the study; 4 questionnaires) weeks.

The endpoints to be measured are as followed:

- Scores of the individual items of the questionnaires;- Mean score of the questionnaires;- Differences between the average score values of the individual questionnaires at the different survey times.

The experience of using the app and the virtual coach (REA) and using the intervention itself will be assessed through a semi-structured interview. The endpoints to be measured are qualitative.

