The User Engagement Scale Short-form (28) is a short self-report questionnaire to assess user engagement with a digital solution. This measure includes 12 items based on a 5-point Likert scale, ranging from 1 (strongly disagree) to 5 (strongly agree). The questionnaire consists of 4 factors: (1) focused attention, which indicates the feeling of being immersed in the interaction; (2) perceived usability, which is the negative effect experienced due to the interaction and the effort expended; (3) aesthetic attractiveness, which represents the graphical and visual appeal to a digital solution; (4) the reinforcement factor (reward). The latter is a single factor that includes duration, which evaluates the overall success of the interaction; novelty, which examines the general interest related to the interaction with a digital solution; and, finally, the perceived engagement factor, which evaluates the overall enjoyment of the interaction. This questionnaire was not translated into Italian and was, therefore, translated through the Back Translation procedure.

The User Mobile Application Rating Scale (31) is a tool for assessing the quality of mobile apps and its functionalities. It is characterized by a 20-item measure that includes 4 objective quality subscales (engagement, functionality, aesthetics, and information quality) and 1 subjective quality subscale rated on a 5-point Likert scale, ranging from 1 (poor) to 5 (excellent). The total and subscales scores have very high Cronbach alpha coefficients (.90 and.78-.80, respectively). The scale has been also validated in an Italian context (38).

Psychologists from the project team will conduct the interviews. The interviews are structured with *ad hoc* items to purposively capture specific characteristics of the study and participants’ experiences (39). This interview will be carried out two months after the birth, will last approximately 20 minutes and, with the woman’s consent, will be audio-recorded to allow subsequent analysis.

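### The only stated interview analysis selects answers that recur, so it does not bring out a distressing reaction voiced by one woman, although emotional responses belong to a primary objective

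*Protocol article*

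**What the plan says.** Section 1.3 makes the interview the instrument for primary objective 2, which covers "participants’ experience with both REA and the application, as well as their emotional responses throughout the intervention". Section 2.4.1 describes this part of the primary outcome in one line: "The endpoints to be measured are qualitative".

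Section 2.7.2 is a single sentence. It states that text mining "will be used to extract the answers that appear repeatedly from the interviews", and it extends this to the women's feelings, "with respect to how they felt throughout the process". It gives no recurrence threshold and no separate step for answers given once.

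Participation in the interview is optional: under section 2.1, "women who have given consent will be undergoing a semistructured interview". The number of interviews is not stated. Section 2.5 says that each interview lasts about 20 minutes, is conducted by the project's psychologists and, with consent, "will be audio-recorded to allow subsequent analysis".

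Section 3.1 lists "emergence or worsening of symptoms during the intervention" among the possible critical issues.

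**The concern.** Recurrence is a sensible filter for common usability themes. It fits badly the part of the objective that concerns emotional responses, because a strong negative reaction to psychological content may be uncommon and still important. With at most a few dozen interviews, an uncommon reaction may well be voiced once. An analysis that looks for repeated answers can then give the same thematic result whether no interviewee was distressed or one was.

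At stake is the primary qualitative result, which would lean towards common answers. The developers would also lose information that they need before the randomised trial announced in the Discussion. This goes beyond detail that a condensed article leaves out: the article states a selection criterion, and the criterion does not fit part of the objective.

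**Working it through.** **1. Objective against analysis.** Section 1.3 asks about emotional responses. Section 2.7.2 answers with one method, selection by recurrence, and applies it to feelings as well as to the experience of using REA. No section says that an answer given once is coded, kept in the results or reported. The citation does not settle it: section 2.7.2 cites reference 35 for text mining, while section 2.5 uses reference 35 for the Italian adaptation of the MPFI. The method therefore cannot be traced from the text.

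**2. What else could show distress.**
- CES-D: given at week 0 and at the end of the study, and two months after birth if the woman is willing. It asks about symptoms in the last week.
- Whooley questions: repeated two months after birth. They ask about the last month.
- UES-SF: given at the end of the study. One factor concerns negative effects of the interaction and the effort spent, and individual item scores are an endpoint.
- Clinical escalation (section 3.1): a mitigation, not a stated reported outcome.

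These can register symptoms or a poor experience with the tool. None records an emotional reaction to the content of the sessions.

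**3. Size.** The plan gives no figure to reproduce on this point. Section 2.6 bounds the number of interviews: 50 women recruited, and 50 × (1 − 0.20) = 40 after the planned drop-out. Assumptions: n = 20 to 50 interviews, a true rate p of voiced reactions of 1% to 10%, women independent of each other, and a repeated answer meaning one given by at least two women.

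The part that the recurrence criterion can lose is the case of exactly one voice:

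P(X = 1) = n × p × (1 − p)^(n − 1)

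At p = 0.05:
- n = 20: 20 × 0.05 × 0.95^19 = 0.377
- n = 30: 30 × 0.05 × 0.95^29 = 0.339
- n = 40: 40 × 0.05 × 0.95^39 = 0.271

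P(X = 1) over the assumed range:

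| n | p = 1% | p = 2% | p = 5% | p = 10% |
|---|---|---|---|---|
| 20 | 0.165 | 0.272 | 0.377 | 0.270 |
| 30 | 0.224 | 0.334 | 0.339 | 0.141 |
| 40 | 0.270 | 0.364 | 0.271 | 0.066 |
| 50 | 0.306 | 0.372 | 0.202 | 0.029 |

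**4. Separating what no analysis can recover.** If no interviewee mentions the reaction, no extraction method helps. At p = 0.05, P(X = 0) = 0.95^n is 0.358, 0.215 and 0.129 for n = 20, 30 and 40. Adding P(X = 1) gives P(X ≤ 1) = 0.736, 0.554 and 0.399. Only the P(X = 1) part is due to the criterion. Among samples in which at least one woman voices the reaction, the share with a single voice, P(X = 1) / (1 − P(X = 0)), is 0.588, 0.432 and 0.310.

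**The case against.** The strongest reply is that section 2.7.2 says less than a critic may read into it. It does not say that only repeated answers are used, sets no threshold and describes no discarding. A reader might infer that a single distressing answer is excluded by rule. The text does not support that: it is silent on single answers. The full protocol may also contain a richer qualitative plan.

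A reader might further infer that the study would end up reporting no adverse emotional response when there was one. That does not follow either. Psychologists hear every interview, recordings stay in the source data where the woman agrees, CES-D and UES-SF item scores are endpoints, and the article commits to reporting all results and to publishing whatever they are.

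Finally, a reader might take the combined figures of 74%, 55% and 40% as the loss at a 5% rate with 20, 30 and 40 interviews. They overstate it, because they include the samples in which nobody mentions the reaction.

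All of this limits the point without removing it. The one criterion that the article states is frequency, and it is applied expressly to feelings. General reporting commitments do not help with an answer that the analysis never brought out, and the symptom and usability scales address a different question.

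**Conclusion.** The point holds in a limited form. As written, the only stated interview analysis favours common answers and does not provide for a distressing reaction voiced by one woman, although emotional responses are part of a primary objective. At an assumed rate of 5%, with a repeated answer taken to mean at least two women, the chance of exactly one voice is about 38%, 34% and 27% with 20, 30 and 40 interviews. At a 10% rate it falls to 27% with 20 interviews and about 7% with 40. A stricter threshold than two women would miss more. The consequence is confined to the interview result. It does not show that distress would go unnoticed in the study as a whole.

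**What to change.** In section 2.7.2, keep text mining for common themes and add a sentence such as: *All negative, distress-related or discontinuation-related answers will be coded from a full read of the transcripts and reported as counts by category, including those given by one woman.* Counts by category, with careful wording, can meet the commitment in section 2.8 to anonymous, aggregated reporting. Correct the text-mining citation in the same edit.

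The cost is one sentence, some extra reading of interviews of about 20 minutes each, and care that an isolated answer from a small single-province sample does not identify a woman. No new data collection is needed.
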